### Interventions

As this is a pragmatic study, trial medications will be prescribed open-label and no measures will be taken to intervene with patients’ medication adherence. Trial clinicians will be advised to keep patients’ existing antidepressant treatment(s) at a stable dose within the therapeutic range, as defined in the MPG and BNF [33, 34]. The following recommendations for titration and dosing of each of the two treatment arms will be provided, in line with current best practice guidelines [33, 34]. However failure to adhere to these guidelines will not constitute a protocol deviation:
*Lithium arm:* lithium carbonate/citrate, added on to the current antidepressant. The dose should be adjusted to achieve a serum-lithium concentration of 0.4–1.0 mmol/l 12 h after a dose. Serum level checks should be performed on days 4–7 of treatment and be repeated every week until dosage has remained constant for 4 weeks aiming for an optimal therapeutic plasma level of 0.6–1.0 mmol/l [22, 33].
*Quetiapine arm:* quetiapine fumarate (XR or immediate release formulation) added on to the current antidepressant, taken once daily before bedtime. Recommended dose titration: 50 mg on days 1 and 2 and 150 mg on day 3, aiming for a dose of 300 mg/day by week 2, if tolerated. Thereafter, flexible dosing will follow in the range 150–300 mg/day according to tolerance (as per Bauer et al. 2013) [23]. In elderly patients (>65 years old), the dose titration protocol should be: 50 mg/day on days 1–3, increasing to 100 mg/day on day 4, 150 mg/day on day 8 and 300 mg/day not before day 22 of treatment, if required.

Dosing regimens may need to be altered in the case of concomitant administration of drugs that interact with either quetiapine or lithium.

The initial prescription of a study medication and any essential pre-prescription safety checks must be overseen by a trial clinician. This is followed by a fully flexible continuation phase for up to 52 weeks post-randomisation, in which treatment is shared between primary and secondary care as appropriate according to standard NHS practice in the relevant trust.

In this trial, patients will be randomised to *the decision* to prescribe either lithium or quetiapine. This means that in each case, the treating trial clinician will decide whether or not to prescribe the medication that the patient has been randomised to, according to their clinical judgement. It is therefore possible that a small proportion of randomised patients will not receive the medication that they are allocated to. This may be due to a previously unknown contraindication to the study medication arising during the pre-prescribing safety checks (exclusion criteria for trial entry is *known* contraindications to lithium or quetiapine only). The required safety checks are: electrocardiogram, if clinically indicated (both treatment arms) and pre-lithium blood tests (renal function, thyroid function, full blood count, serum calcium). These tests must be conducted prior to prescription, unless they have been completed within a sufficiently recent period according to the prescribing clinician’s judgement.

All patients will be followed up for 12 months, regardless of medication status. It is expected that a significant proportion of patients will fail to respond or tolerate the medication and will terminate treatment before 12 months. Treatment may also be extended beyond the follow up period at the discretion of the patient’s clinician. All concomitant pharmacological and non-pharmacological interventions are permitted throughout the duration of the trial and will be recorded by the trial team.

*MINI 7.0* Mini International Neuropsychiatric Interview, Version 7.0, *MDD* major depressive disorder, *HDRS* Hamilton Depression Rating Scale – 17 items, *MSM* Maudsley Staging Method, *MÅDRS* Montgomery-Åsberg Depression Rating Scale, *CGI* Clinical Global Impressions, *IDS-C* Inventory of Depressive Symptomatology – Clinician Rated, *HCL-16* Hypomanic Checklist – 16 items, *FIBSER* Frequency, Intensity and Burden of Side Effects Ratings, *PRISE* Patient Rated Inventory of Side Effects, *EQ-5D* EuroQol-5D health index, *THINC-it* THINC-it tool for cognitive dysfunction in Major Depressive Disorder, *DSCT* Digit Symbol Coding Test, *WSAS* Work and Social Adjustment Scale, *ASRM* Altman Self-Rating Mania Scale, *VAS* Visual Analogue Scale, *GAD-7* Generalised Anxiety Disorder questionnaire – 7 items, *SAPAS* Standard Assessment of Personality: abbreviated Scale, *CSRI* Client Service Receipt Inventory, *FBC* Full blood count, *U&Es* Urea, electrolytes and creatinine, *LFTS* Liver function tests, *TFT* Thyroid function tests

^a^ Optional and/or collected in a subset of participants

^b^ Measures solely for tertiary and ancillary analyses

**Fig. 1 Fig1:**
[figure not shown]
Flow Chart of Trial Procedures

### Screening visit

All participants must provide written informed consent at the start of the screening assessment. Consent may be taken by a trial clinician, or delegated non-clinical researcher with trust approval. Confirmation of eligibility will be signed off by a trial clinician at the end of this assessment.

### Baseline, weekly monitoring and follow up visits

If the baseline assessment is more than 7 days after the screening visit, the screening assessments (excluding demographic information) will be repeated to ensure that the participant still meets the required eligibility criteria. Randomisation will be conducted at Week/Time Point 0, which is the day of the baseline visit. Follow-up assessments with trial researchers will be conducted at 8 (+ − 1) weeks, 26 (+ − 2) weeks, and 52 (+ − 2) weeks post-randomisation.

Patients will also be asked to complete three questionnaires weekly via the True Colours system (https://truecolours.nhs.uk): the QIDS-SR, WSAS, and study specific questions about medication status. True Colours is an online monitoring tool on which questionnaires can be completed via email, text, or by logging on to the website. For patients without internet access, a paper version can be provided. Automated reminders will be sent to participants on a day and time of their choosing.

Optional study blood tests will be conducted at baseline, 8 and 52 week visits (agreement to clinical blood tests throughout the trial duration is not optional). Optional blood tests include samples for genetic and cytokine analysis, along with hair samples to assess cortisol levels, and saliva samples for genetic analysis where blood samples are not provided. This will be done in collaboration with the Biomedical Research Council (BRC) BioResource. Further optional measures include a qualitative interview exploring patient experience of True Colours as a mood monitoring tool (conducted at one follow up appointment) and the THINC-it tool for cognitive function [46].

One section of the CSRI collects data about the patient’s principal formal or informal carer. Where applicable, the carer can complete this questionnaire following their provision of written informed consent. Where this is not possible, responses from the patient will be accepted.

At 4 weeks post-randomisation, participants will receive a phone call from a trial researcher to determine the date they began taking their allocated medication. If applicable, the reason the patient has not commenced their medication will be recorded and this question will be repeated at follow-up visits to determine if a patient has subsequently begun the allocated medication.

All study data will be stored on a custom-designed, online data entry system which is compliant with Good Clinical Practice guidelines, and created and maintained by King’s Clinical Trials Unit (InferMed MACRO version 4.0). The system is programmed to perform validation checks for data quality purposes (e.g. range checks to avoid data entry errors) and flags out of range or missing data for monitoring purposes. It also has a built in audit trail to aid data monitoring.

### Statistical methods for analysing primary and secondary outcomes

A full statistical analysis plan will be drawn up prior to completion of data collection. The main analysis will follow an intention to treat (ITT) principle, whereby patient data are analysed by treatment group, regardless of the medication status of patients throughout the follow-up period.

Participant flow will be presented in a CONSORT diagram. For analysis of the listed primary and secondary outcomes, missing baseline data will be filled in using imputation [47]. Models will covary for randomisation stratification factors throughout. For the self-report QIDS-SR score a linear mixed model, covarying by baseline score, will be used for the estimation of the mean treatment difference and 95% confidence interval (CI) over the course of the trial. Full information maximum likelihood methods will be used for analysis, which will account for missing data under the missing at random assumption. Error distributions will be checked using Q-Q plots. Time to discontinuation will be calculated from first prescription date to treatment discontinuation, and will be analysed using Kaplan-Meier methods and Cox regression models, providing the hazard ratio for treatment discontinuation in lithium versus quetiapine, and associated 95% CI.

Continuous secondary outcomes measured over time will use generalised linear models appropriate to the variable distribution covarying by baseline where applicable, and using mixed models where there are repeated measurements. Adjustment for multiple testing will be presented [48].

For measures where missingness is above 5% and where the absence of repeated measurement gives less confidence in the adequacy of the missing data properties of maximum likelihood, we may undertake a sensitivity analysis within a multiple imputation framework [49].

### Power calculation

Based on our power calculation and superiority design, we require 276 patients to be randomised. When considering the sample size required, we have considered both the primary outcome measures of time to all cause treatment discontinuation and longitudinal symptom severity as assessed by QIDS-SR scores. This sample size was calculated based on the following assumptions:
*Treatment discontinuation:* estimated 20% discontinuation from treatments by 8 week follow up visit (as per Bauer et al., 2013) [20]), and 50% treatment discontinuation for lithium and 30% for quetiapine by 52 weeks.
*Missing data:* 40% missingness for each of the post-randomisation QIDS-SR scores was allowed for. While the missingness has been assumed independent over time, the QIDS-SR scores are assumed uniformly correlated with a correlation of 0.6 [47]. We have allowed the discontinuation status at follow-up to be unknown for 10% of the sample.
*Effect size:* The minimum clinically significant difference for outcomes in depression treatment is widely taken to be 3 points on the HDRS [3, 50]. This corresponds to an effect size of 0.38 between treatments. We wish to see a difference of this effect size in the QIDS-SR score sustained over the duration of the trial and so will estimate the effect as an area under the curve.
*Power*: All power calculations are for two-tailed tests and alpha = 0.05.

With a sample size of 276 at baseline and 10% loss to follow up, we expect 248.4 patients to complete the trial. The Stata stpower command gave 90% power using a logrank test to detect a difference in the time to discontinuation with 50% (lithium) and 70% (quetiapine) as the proportions of participants remaining on assigned treatment. This determined the lower limit of the sample size. Applying this sample size to the self-report QIDS-SR data we also needed to account for the likely haphazard nature of missing data points at each assessment time point. We used simulation and the non-central chi-square method. Using 1000 samples, a simple random intercept model covarying for baseline, a time dummy variable and with a single average combined treatment effect, this number of participants will provide 99.7% power to detect an effect size of 0.38 (with 1 degree of freedom, χ^2^ = 3.84, and non-centrality parameter = 20.86).

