### Randomisation and blinding

The study will randomise individual participants 1:1 to the decision to prescribe lithium or quetiapine, stratified by recruiting region (London, Oxfordshire, or North East England), depression severity (HDRS-17), and TRD severity (failure of two / three or more antidepressant treatments in the current episode), using block randomisation with randomly varying block size. Randomisation will be conducted by a trial researcher using an independent online service provided by UK Clinical Research Collaboration registered King’s Clinical Trial Unit, with unique patient identification numbers generated by the InferMed MACRO system.

This is an unblinded study, whereby treating clinicians, trial researchers, and patients will be aware of the treatment allocation for patients where applicable to their role. In order to reduce the potential for assessor bias, the following clinician-rated assessments will be completed at follow up visits by an assessor who is blind to the patient’s medication (face-to-face or via phone): 1) MÅDRS [35], and 2) Clinical Global Impressions scale (CGI) [36]. Trained trial researchers and clinicians may perform blinded assessments, but must not have access to the trial database for the relevant site to reduce the likelihood of unblinding (access to the trial database is granted on a site by site basis, dependent on role). The blinded assessor will remind the participant not to reveal treatment allocation at the start of the assessment and will confirm they remained blinded to treatment allocation throughout the assessment.

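### The 90% log-rank power uses only the week-52 proportions; if the listed 20% week-8 discontinuation applies to each arm, power is about 82–86%

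*Protocol article*

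**What the plan says.** All of the following stands in the Power calculation section of the protocol article, except where noted.

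- Size: "we require 276 patients to be randomised", with "With a sample size of 276 at baseline and 10% loss to follow up, we expect 248.4 patients to complete the trial".
- Test level: "All power calculations are for two-tailed tests and alpha = 0.05".
- Discontinuation, given as one of the assumptions behind the sample size: "estimated 20% discontinuation from treatments by 8 week follow up visit", attributed to a cited head-to-head study, and then "50% treatment discontinuation for lithium and 30% for quetiapine by 52 weeks". The week-52 figures are split by arm; the week-8 figure is not.
- Power: "The Stata stpower command gave 90% power using a logrank test to detect a difference in the time to discontinuation". The only inputs named for this are the shares still on their assigned drug, half on lithium and 70% on quetiapine. The section says that this result set the lower limit of the sample size.
- Analysis (section on statistical methods for primary and secondary outcomes): Kaplan-Meier methods and Cox regression, "providing the hazard ratio for treatment discontinuation in lithium versus quetiapine, and associated 95% CI".

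**The concern.** A log-rank calculation from two end-of-study proportions assumes that the hazard ratio is the same throughout follow-up. The listed assumptions appear to describe something else: no difference between the arms by week 8, and a 20-point difference by week 52. Both patterns end at the same proportions and yield the same number of events, but not the same power. The log-rank test weights all events equally, so early events without a treatment difference add variance and no signal.

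The stakes are the type II error on the first primary outcome. This calculation fixed the sample size; the second primary outcome has a stated power of 99.7%, so it is not the limiting one. The Discussion also says what will be done if the primary outcomes show no significant difference, so the chance of missing a true difference affects how the trial will be read.

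**Working it through.** **Inputs.** From the Power calculation section: 276 randomised; 248.4 evaluable (124 per arm used in simulation); two-sided alpha 0.05; 20% off treatment by week 8; 50% (lithium) and 30% (quetiapine) off treatment by week 52. From Randomisation and blinding: 1:1 allocation. The simulations censor administratively at week 52.

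**Step 1: reproduce the 90%.**
- Constant hazard ratio: ln(0.70)/ln(0.50) = 0.515.
- Expected events: 248.4 × (0.50 + 0.30)/2 = 99.4.
- Schoenfeld: √(99.36/4) × |ln 0.5146| − 1.96 = 4.984 × 0.6644 − 1.96 = 1.35, so power is 91.2%.
- Freedman: √99.36 × (1 − 0.5146)/(1 + 0.5146) − 1.96 = 9.968 × 0.3205 − 1.96 = 1.23, so power is 89.2%.
- Comparison of two proportions: 90.0%.
- Simulated log-rank under proportional hazards (20,000 trials, 124 per arm): 90.5%.

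The plan's figure is reproduced from the week-52 proportions alone.

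**Step 2: add 20% in each arm by week 8.**
- Weeks 0–8: the same survival, 0.80, in both arms, so the hazard ratio is 1.0.
- Weeks 8–52, lithium: 0.50/0.80 = 0.625 of those still on treatment remain.
- Weeks 8–52, quetiapine: 0.70/0.80 = 0.875 remain.
- Hazard ratio after week 8: ln(0.875)/ln(0.625) = 0.284.
- Events at 124 per arm: 24.8 + 24.8 = 49.6 by week 8. After week 8, 0.30 × 124 = 37.2 on lithium and 0.10 × 124 = 12.4 on quetiapine, again 49.6. The total is 99.2, as before, but half of it carries no treatment difference.

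**Step 3: rough hand check.** After week 8, lithium's share of those at risk falls from 0.5 to 0.50/(0.50 + 0.70) = 0.417, on average about 0.458.
- Expected lithium events: 0.458 × 49.6 = 22.7.
- Observed minus expected: 37.2 − 22.7 = 14.5.
- Variance: 49.6 × 0.25 + 49.6 × 0.458 × 0.542 = 24.7.
- Mean z: 14.5/√24.7 = about 2.9, so power is about Φ(2.9 − 1.96), or 83%.

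**Step 4: simulation** (piecewise-exponential survival, two-sided log-rank; 20,000 trials for the first five rows and the 25.8%/14.2% row, 8,000 for the 22%/18% and 20%/10.8% rows).

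| Week-8 discontinuation, lithium / quetiapine | Patients | Power |
|---|---|---|
| Constant HR 0.515, exponential from week 0 | 248 | 90.5% |
| Constant HR 0.515, exponential from week 0 | 276, 10% random loss | 92.2% |
| 20% / 20% | 248 | 82.4% |
| 20% / 20% | 276, 10% random loss | 83.6% |
| 20% / 20% | 276, all observed | 86.4% |
| 22% / 18% | 248 | 85.7% |
| 25.8% / 14.2% (pooled 20%, constant HR) | 248 | 90.6% |
| 20% / 10.8% (lithium 20%, constant HR) | 248 | 90.8% |

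Repeat runs of the 20%/20% case with 248 patients gave between 81.9% and about 83%. A Cox Wald test in that case gave 82.6% (4,000 trials).

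The last two rows come from the constant hazard ratio. With lithium at 20%, quetiapine is 1 − 0.80^0.5146 = 10.8%. For a pooled 20%, remaining proportions of 0.742 and 0.742^0.5146 = 0.858 give (25.8% + 14.2%)/2 = 20%.

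**The case against.** The strongest reply is that nothing was miscalculated. The power sentence names its two inputs, 90% follows from them, and planning a log-rank test from two end proportions is standard practice. The text does not say that the week-8 figure entered that calculation. This stands: a reader might infer a slip in the stpower run, and the document does not support that.

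Second, the week-8 phrase does not say that 20% holds in each arm. It is an estimate from a cited study that is not at hand, and a pooled 20% can be reconciled with a hazard ratio of 0.515. This stands in part. The equal-arm reading is the natural one, because the same sentence separates the arms at week 52 and not at week 8, but it is not the only one. The shortfall also shrinks once exact equality is relaxed, to about 86% power at 22%/18%.

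Third, 248 fully observed patients is the least favourable treatment of the 10% loss, because survival analysis keeps censored time. This is fair, although the plan itself works from 248.4. Every variant of the equal-arm reading computed here is below 90%.

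Fourth, one might go on to ask for hazard ratios by period, or for restricted mean time on treatment, beside the Cox estimate. That belongs to the statistical analysis plan, which is not shown, or is a matter of preference. Kaplan-Meier methods are already planned, so a late separation of the curves would be visible. It is no part of this point.

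**Conclusion.** The listed assumptions and the stated power do not agree on the plain reading of the week-8 figure. If 20% applies to each arm, power for time to discontinuation is about 82–83% with 248 evaluable patients, about 84% with 276 randomised and 10% random loss, and about 86% with all 276 observed. The corresponding type II error runs from about 18% down to about 14%, against the stated 10%. These figures assume a constant hazard within each of the two periods and censoring at week 52.

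The 90% is compatible with the week-8 figure only if the week-8 rates differ by arm about as a hazard ratio of 0.515 requires, for example about 26%/14% or 20%/11%.

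A reader might infer that the trial is underpowered or too small. The figures do not support that: power exceeds 80% in every scenario computed. Nor is it right to say without qualification that the type II error is nearly doubled; that describes only the lower end of the range, and only the equal-arm reading. The point is moderate: a figure that set the sample size is overstated under the plain reading of its own assumptions, while the trial's size, test and error level are otherwise unaffected.

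**What to change.** Do one of two things in the Power calculation section:

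1. If 20% by week 8 was meant for each arm, restate the log-rank power for time to discontinuation as about 82–86% under the listed assumptions, and say how the 10% with unknown status is handled.
2. If it was meant as a pooled or lithium-only figure, give the week-8 discontinuation by arm in a form consistent with a hazard ratio of 0.515, and keep 90%.

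Either is a change of one or two sentences. No further patients and no change to the analysis are needed. The only cost is that the first option makes the stated power less favourable.

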### Monitoring

There is no planned interim analysis and no specific “stopping rules” for the study. We have an independent Data Monitoring and Ethics Committee and an independent Trial Steering Committee. SAEs will be reported to the relevant bodies for all patients throughout their involvement in the trial. Clinicians have the right to discontinue the study drug in the event of identified contraindications, inter-current illness, pregnancy, adverse drug reactions, adverse events, protocol violations, administrative causes, or for other reasons. We will adhere to NHS confidentiality practice, and to the Research Governance Framework in monitoring, auditing and managing the research.

## Discussion

This protocol paper describes a pragmatic randomised clinical trial designed to determine whether the decision to prescribe quetiapine is more clinically and cost effective than lithium for patients with TRD over 12 months. The chronicity of TRD, in which patients often fluctuate between states of remission and relapse [51], highlights not only the importance of this research question, but also the implementation of a 12 month follow up period. As discussed, there have been no direct head-to-head comparisons of these treatments with a follow up period of greater than six weeks. This is insufficient given that up to 80% of patients with TRD relapse within 12 months of responding to treatment [8, 20]. Our choice of primary outcome, a longitudinal measure of depression severity (QIDS-SR), measured weekly over 12 months via the True Colours system (www.truecolours.nhs.uk), recognises the highly fluctuating nature of this disorder. True Colours has been used to assess mood in prior research studies with success [52] and facilitates the monitoring of all cause treatment discontinuation across the full duration of the trial.

The benefits of determining whether one of these recommended and widely prescribed medications is more effective for patients with TRD are clear. However the results of this study should also positively impact secondary care mental health teams and the wider NHS by helping to minimise relapse rates and in doing so alleviate some of the financial and time burden placed on mental health services. If there is no significant difference between lithium and quetiapine in the primary outcomes of clinical effectiveness, the cost-effectiveness analysis, which takes into account the different monitoring requirements for these medications, may benefit health bodies by informing them of the most cost-effective of these two treatment options. In addition, our further analyses may contribute to the growing body of research examining predictors of treatment response in depression, and the development of personalised mental health care.

The potential impact of this trial is maximised by its pragmatic design, which ensures that the results will be directly applicable to real-world clinical practice. The PRECIS-2 tool [51] was used to assess how far we have achieved this and what elements of the design are most pragmatic. A key pragmatic strength is our choice of primary outcomes (the effectiveness and tolerability of the treatments) which are directly applicable to, and can clearly be understood by, the patient group. Additionally, our broad inclusion criteria and minimal exclusion criteria enable us to capture as much variation in the TRD population as possible and include the majority of patients that are likely to receive such an augmentation therapy in routine clinical practice. Examples of this are the inclusion of patients demonstrating suicidal ideation, as this group is often excluded from clinical trials, and the decision not to include an upper age limit (commonly set at 65 years for TRD clinical research) improving the applicability of our results to older patients [3]. Furthermore, alongside the recruitment of patients from secondary care settings, where lithium or atypical antipsychotic augmentation is commonly initiated, we are also recruiting patients from primary care. In doing so we are ensuring that our samples reflect the range of patients that should be considered for these two augmentation therapies according to best practice guidelines.

The pragmatic design of the trial is also reflected in our decision to not dictate a specific dosing or monitoring schedule. As discussed, clinicians are provided with best-practice dosing and monitoring guidelines, but are free to prescribe, monitor and discontinue the trial medication as they find clinically appropriate.

The PRECIS-2 tool also highlighted some necessary limitations to the trial’s pragmatism; primarily the large number of measures conducted during the follow up period. As with all pragmatically designed trials, there must be a balance between the need for adequate data collection and the additional burden this places on participants, beyond what would be experienced in normal clinical practice. However, all chosen measures were deemed necessary by the study team to ensure that the results of the trial aid the development of a modified and evidence based treatment pathway for TRD, and contribute to the improvement of treatment outcomes in this patient group. Conducting a thorough psychiatric history assessment to determine TRD staging and depression characteristics, assessing personality traits relating to refractoriness, evaluating mixed and atypical depressive symptomatology, and collecting biological samples to examine genetic and inflammatory markers and changes in physical health, will allow for a thorough comparison between the two treatments. In order to minimise patient dropout, some of the measures associated with tertiary or ancillary outcomes only have been made optional for participants. Additionally, information will be gathered from medical records or at future follow up visits where possible should a patient fail to attend or complete an assessment.

The LQD study is a large scale trial designed to build on evidence reported by previous short term comparisons of lithium and quetiapine augmentation in patients with TRD [21, 22]. In doing so, we hope to definitively determine which of these two augmentation treatments (if either) should be preferential over the other, improving patient outcomes and minimising the burden that TRD places on clinical resources.

